**4.2 Secondary outcomes**

Change in the following data during the intervention period

1) body weight, waist, blood pressure, body fat, abdominal visceral fat

2) IMT (Intima Media Thickness)

3) CAVI (Cardio Ankle Vascular Index)

4) AST, ALT, gamma-GTP, HbA1c, glycoalbumin, Total cholesterol, HDL cholesterol,

LDL cholesterol, tPAI-1, hs-CRP, adiponectin, leptin, ADMA, lipid metabolites

5) mRNA expression of M1/M2 phenotype of PBMC (TNF-alpha, MCP-1, CD11c,

CD163, HO-1)

6) meal tolerance test (0, 30, 60, 90, 120min): glucose, insulin, triglyceride, free fatty

acid, glucagon, GLP-1, GIP

7) Urine 8-isoprostan, creatinine

8) bacterial flora

[figure not shown]
9) change in the eating behavior and psychosomatic state by questionnaire

| Dietary assessment | ○ | ○ | ○ |  |  |
| --- | --- | --- | --- | --- | --- |
| Dietitian guidance | ○ | ○ | ○ |  |  |
| Body weight | ○ 1) | ○ | ○ | ○ | ○ 1) |
| Visceral fat volume |  | ○ | ○ | ○ |  |
| IMT |  | ○ |  |  |  |
| CAVI |  | ○ | ○ | ○ |  |
| Blood test | ○ 1) | ○ | ○ | ○ | ○ 1) |
| Urine test |  | ○ | ○ | ○ |  |
| Bacterial flora |  | ○ | ○ |  |  |
| Endothelial function |  | ○ | ○ | ○ |  |
| Meal tolerance test |  | ○ | ○ | ○ |  |
| Questionnaire | ○ | ○ | ○ |  | ○ |

1) These information will be collected from charts.

Figure 2. Data collections

**5 Preservation of the specimen**

Preservation of the specimens as listed below are planned for further analysis that is not identified at the time of obtaining consent from the research subject. Samples will be kept for 5 years at -80ºC. Subjects have a chance to see newly published protocol and have a right to disagree further analysis.

1) Plasma 1ml X 5 vials *

2) Serum 1.5ml X 2 X 5 vials *

3) Urine 2ml X 3 vials

* All samples are left-over from tests for secondary outcomes. No additional blood drawing will be planed.

**6 Statistical analysis**

The peak forearm blood flow (FBF) response, duration of reactive hyperemia (RH), and total reactive hyperemic flow (flow debt repayment (FDR)) will be used to assess the resistance of vessel endothelial function. Changes in endothelial function will be analyzed by paired t-test. Differences in change of endothelial function will be analyzed by unpaired t-test.

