**3.2.1 Rationale for setting the number of patients**

We calculated our sample size using results from a preliminary study, in which an intervention of a brown rice diet increased FDR* by 83.1 ± 60.2% and a white rice diet increased FDR by 19.5 ± 40.9% (unpublished data). We estimated that with a sample size of 30, the study would have 80% power to detect differences in the outcome between randomized groups, assuming an overall lost-to-follow-up rate of 14% with a type 1 error of 5% (two-sided).

* flow debt repayment: one of the endothelial function

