**3.11 Randomization**

Randomization will be stratified by minimization method with age (66 years old), sex, and body mass index (24). After the run-in period, participants will be randomly assigned to a brown rice or white rice diet. Investigators will be provided with a random allocation sequence that will be made by a research assistant, who is independent of the investigators, using computer-generated random digits.

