**4 Outcomes**

Change in outcomes between 2 month and 0 month. In addition carryover effect will be analyzed at 4 month.

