**4.1 Primary outcomes**

The primary outcome of the present study is change in endothelial function both in fasting and in postprandial state.

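### The between-arm t-test on change uses neither the month-0 value nor the minimisation factors: it is valid and adequately powered, but gives up precision that costs almost nothing to recover

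*Protocol*

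**What the plan says.** Section 6 of the protocol names two tests for endothelial function. Within an arm: "Changes in endothelial function will be analyzed by paired t-test". Between arms: "Differences in change of endothelial function will be analyzed by unpaired t-test". Neither sentence names a covariate or a scale.

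The outcome is defined in section 4 as "Change in outcomes between 2 month and 0 month", and section 4.1 makes the primary outcome "change in endothelial function both in fasting and in postprandial state". Section 6 lists three indices: peak forearm blood flow, duration of reactive hyperemia, and flow debt repayment (FDR).

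On allocation, section 3.11 says "Randomization will be stratified by minimization method with age (66 years old), sex, and body mass index (24", where 66 and 24 are the cut-points. The same section adds: "Investigators will be provided with a random allocation sequence that will be made by a research assistant".

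The sample size in section 3.2.1 is built on percent increases in FDR from a preliminary study: 83.1 ± 60.2% on brown rice, while "a white rice diet increased FDR by 19.5 ± 40.9" percent.

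The data-collection table in section 4.2 has a row "Endothelial function" marked at three time points, and a month-0 value is needed in any case to form the change.

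**The concern.** Three things come together.

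- **Baseline.** When r is below 1, a change score is correlated with its own starting value, so a chance difference between arms at month 0 carries into the estimate. Endothelial function is not an allocation factor, so nothing in the design limits such a difference at 15 per arm. Conditioning on the month-0 value removes this and usually reduces the variance.
- **Allocation factors.** Minimisation on prognostic factors makes the arms more alike than simple randomisation would. A t-test that ignores the factors still charges their variance to error, so its standard error is too large.
- **Scale.** The sample size is in percent increase, while sections 4 and 6 say only change. Absolute and percent change are different quantities and can give different p-values, so a choice on the primary test is left open.

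At stake are wider confidence intervals and less power than the same 30 patients can give. This is not something deferred to an unseen analysis plan, because the protocol itself fixes the test.

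**Working it through.** **Inputs from the protocol.** Means 83.1 and 19.5, SDs 60.2 and 40.9, 80% power, two-sided 5%, 14% loss to follow-up, 15 per arm (sections 3.2 and 3.2.1). **Assumed, because the protocol does not give them:** r, and R², the share of variance in the change explained by age, sex and BMI.

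**1. Reproduce the sample size.** Difference = 83.1 − 19.5 = 63.6. SD = √[(60.2² + 40.9²)/2] = 51.46. Standardised effect = 63.6/51.46 = 1.236. The normal approximation needs 11 per arm, or 13 after dividing by 0.86 (26 in total). The noncentral t needs 12 per arm, or 14 after dividing by 0.86 (28 in total). The stated 30 is within 2 of the latter, so the sample size is not in dispute.

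**2. Power of the planned test.** 30 × 0.86 = 25.8, taken as 13 evaluable per arm. With 24 degrees of freedom the t-test has 85.6% power.

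**3. Add the month-0 value.** With common variance s² at both visits:

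- Var(change) = 2s²(1 − r)
- Var(ANCOVA) = s²(1 − r²)
- Ratio = (1 + r)/2

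Estimating q covariates in N patients inflates the variance by about 1 + q/(N − q − 3). At N = 26 this is 1 + 1/22 = 1.045 for baseline alone (23 degrees of freedom) and 1 + 4/19 = 1.211 for all four covariates (20 degrees of freedom). The last column below takes age, sex and BMI to explain nothing and to be no better balanced than by simple randomisation, so it is a worst case.

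| r (assumed) | Variance ratio | t-test on change | ANCOVA, baseline only | ANCOVA, four covariates, worst case |
|---|---|---|---|---|
| 0.3 | 0.65 | 85.6% | 95.5% | 92.2% |
| 0.5 | 0.75 | 85.6% | 92.6% | 88.2% |
| 0.7 | 0.85 | 85.6% | 89.3% | 84.0% |
| 0.9 | 0.95 | 85.6% | 85.7% | 79.8% |

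Minimisation balances the three factors, so the real penalty is smaller than the last column charges. Simulation with N = 26, three non-prognostic binary factors and an assumed biased-coin probability of 0.9 gives the four-covariate model about 95%, 91% and 88% at r = 0.3, 0.5 and 0.7.

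**4. Effect of omitting the minimisation factors.** The large-sample formula under perfect balance, 2[1 − Φ(1.96/√(1 − R²))], gives a true type 1 error of 3.9%, 2.8% and 1.9% at R² = 0.1, 0.2 and 0.3. Balance is imperfect at N = 26, so simulation is the better guide. With the same biased coin, one simulation gives 5.0%, 4.5%, 3.6% and 2.6% at R² = 0, 0.1, 0.2 and 0.3, while the model adjusted for the three factors stays at about 4.6% to 5.5%. Simulations run separately put the R² = 0.2 value at about 3% to 3.6%. At R² = 0.3 the mean t-test standard error is 0.391 against a true 0.338 in SD units (0.391/0.338 = 1.16, so 16% too large). Power there is 88.6% unadjusted and 94.4% adjusted.

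**The case against.** The strongest reply is that nothing is broken. Under randomisation the unpaired t-test on change is unbiased, it matches the outcome as section 4 defines it, and it exceeds the stated 80% power. That stands: what is left is efficiency.

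Four stronger readings are tempting, and the protocol does not support them.

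- **That ignoring the minimisation factors makes the test unsafe.** The mismatch only makes it conservative. It also needs two conditions. Minimisation must actually have been used, and section 3.11 also describes a ready-made random sequence, which sits badly with minimisation and must be reconciled. The factors must also predict the change: steady effects of age, sex and BMI on level cancel in a change score, and the protocol gives no R².
- **That ANCOVA wins whenever r is below 1.** This is a large-sample statement. Here baseline-only adjustment breaks even near r = 0.9. In the worst case the four-covariate model breaks even near r = 0.65, since (1 − 0.65)/2 is about 0.17, the variance reduction needed to repay the factor 1.211. The simulated 88% at r = 0.7 shows that this bound is pessimistic, but the gain can still vanish at high r.
- **That the pilot figures require a log scale.** The post/pre ratios do have similar coefficients of variation (0.602/1.831 = 0.329 and 0.409/1.195 = 0.342), while the SDs differ 1.47-fold. But these are two SDs from an unpublished study of unstated size. An F-test of that SD ratio would give p = 0.26 with an assumed 10 per arm and 0.10 with 20. They also concern FDR only, not the other two indices.
- **That sections 3.2.1 and 6 contradict each other on scale.** Section 6 never says absolute change, and percent change is one possible reading. It is an ambiguity.

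**Conclusion.** The point holds as one of precision. The planned test is valid and meets its stated power, but it leaves out information already collected. Adding the month-0 value raises power at 13 per arm from 85.6% to about 95.5%, 92.6% or 89.3% at r = 0.3, 0.5 or 0.7, and by almost nothing at r = 0.9. This is the firm part. Adding the allocation factors aligns the analysis with the allocation. It recovers a type 1 error of about 3% to 3.6% (at an assumed R² of 0.2) to about the nominal 5%, but only if minimisation was used and the factors are prognostic.

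The figures rest on an assumed r and R², on equal variances at the two visits, and on carrying the standardised effect of 1.236, which comes from percent increases, over to a change score. The ratio (1 + r)/2 is for absolute change, and no gain has been worked out on the percent scale. A reader should not infer inflated false positives or an underpowered trial. The improvement is worth making, but the plan does not fail without it.

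**What to change.** In section 6, replace the unpaired t-test by ANCOVA of the 2-month value on arm, the matching month-0 value, age (<66/≥66), sex and BMI (<24/≥24). Use it for each endothelial index and for both the fasting and the postprandial state, so that the primary outcome in section 4.1 is left as it is. Report the adjusted difference with a 95% confidence interval, and keep the unpaired t-test as a sensitivity analysis.

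Three clarifications belong with it:

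- State one scale for the change, so that it agrees with the percent increase in section 3.2.1. A log scale reported as a ratio is a reasonable option, but the pilot SDs do not prove that it is needed.
- Say in section 3.11 whether allocation is by minimisation or from a ready-made sequence.
- Confirm that the month-0 postprandial value is a true baseline. Section 3.8 can be read as giving each arm its own rice at the test before the intervention. If postprandial endothelial function is measured at that test, the value may already differ by arm, and the fasting month-0 value would be the safer covariate.

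The cost is wording and 4 residual degrees of freedom out of about 24, with no new data or patients. If r is high and the factors are not prognostic, there is little or no gain, and possibly a small loss.

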**7 Discontinuation criteria for individual patients**

1. The principal investigator or sub-investigator determine that the study should be discontinued due to sick days etc.
2. Withdrawal of consent
3. Difficulty in continuation of dietary intervention

The principal investigator or sub-investigator needs to report a reason and exact date of discontinuation, and collect basic information at this time point.

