**Effects of brown rice or white rice on glycemic and lipid metabolism, and vascular function**

**1 Background**

We have been reported that high-fiber diet intervention with combination of brown rice and fiber-rich dishes improve endothelial function in patients with type 2 diabetes mellitus (T2DM)1,2. However, it remains unknown whether brown rice is an essential factor to improve endothelial function in these patients. In this study we hypothesized that a simple dietary intervention with brown rice will be acceptable dietary intervention in out-patients and improve vascular function through change in glycemic and lipid metabolism.

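### Section 7 lets participants who find the assigned diet difficult leave without a month-2 endothelial measurement, so loss of the primary outcome may differ by arm

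*Protocol*

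**What the plan says.** Protocol section 7 gives three grounds for discontinuing an individual patient: the investigator's decision, withdrawal of consent, and "Difficulty in continuation of dietary intervention". The first ground speaks of discontinuing the study, so the list is most naturally read as reasons for leaving the trial and not only for stopping the rice. For all three grounds the data requirement is the same: the investigator "needs to report a reason and exact date of discontinuation, and collect basic information at this time point". Basic information is not defined, and no section asks for later visits in these patients.

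Sections 4 and 4.1 define the primary outcome as the change in endothelial function, fasting and postprandial, between month 0 and month 2. Section 6 compares the changes between arms by unpaired t-test. Section 3.2.1 deals with losses only through the sample size, "assuming an overall lost-to-follow-up rate of 14" per cent, without a split by arm or by reason. Section 3.5.1 makes the trial open-label. Section 3.1 excludes patients who have eaten brown rice. The hypothesis in section 1 includes that "a simple dietary intervention with brown rice will be acceptable dietary intervention in out-patients".

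**The concern.** Stopping the diet and leaving the study are written as one event. A change score needs both values, so a patient who leaves before month 2 has none. If basic information happened to include endothelial function, it would be measured on the day of stopping and not at month 2.

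The exit reason is tied to the treatment. Participants know which rice they have been given, and by the exclusion criterion one of the two foods is new to them. The run-in of section 3.6.1 assesses tolerability on a standard diabetes diet before randomisation and does not mention the study rice, so it does not screen for difficulty with brown rice. Loss could therefore be unequal between arms and related to outcome. The t-test would then compare two groups that randomisation no longer makes alike. The patients lost would also be the ones who bear on the acceptability part of the hypothesis.

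This cannot be left to an analysis plan. Such a plan can choose an analysis set or impute, but it cannot recover measurements that were never taken.

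**Working it through.** **Inputs, all from Protocol sections 3.2 and 3.2.1.** Expected change in flow debt repayment (FDR): brown rice 83.1% (SD 60.2), white rice 19.5% (SD 40.9). Two-sided alpha 5%, power 80%, 15 per arm, 14% lost overall.

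**1. The plan's own figure.**
- Difference = 83.1 − 19.5 = 63.6.
- Common SD = √((60.2² + 40.9²)/2) = 51.46.
- Standardised effect = 63.6/51.46 = 1.24.
- The t-test needs 11.3 per arm, so 12. Allowing for loss, 12/0.86 = 13.95, so 14 per arm or 28 in total.

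The stated 30 is therefore reproduced with a small margin. With 13 completers per arm, power is 85.6%. The expected losses are covered for power. Sample size does nothing about bias.

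**2. Expected losses.** 0.14 × 30 = 4.2, about four patients, for any reason and in either arm.

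**3. Illustrative bias from unequal loss.** Suppose a fraction f of one arm is lost, none of the other, and those lost differ from completers by g SD. The completer mean, and so the difference, shifts by f × g × 51.46. The values of f and g are assumptions; the protocol gives neither.

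| Lost from one arm | Gap | Shift (points) | Share of 63.6 |
| --- | --- | --- | --- |
| 2 of 15 | 0.5 SD | 3.4 | 5% |
| 2 of 15 | 1 SD | 6.9 | 11% |
| 4 of 15 | 0.5 SD | 6.9 | 11% |
| 4 of 15 | 1 SD | 13.7 | 22% |

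With no true effect and four losses against none, simulation puts the two-sided type I error at about 6.1% (gap 0.5 SD) or 10.0% (gap 1 SD) instead of 5%. If losses and gaps are equal in both arms, the shifts cancel and the bias in the difference is about zero.

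**4. A separate question: dilution.** Suppose patients who stop brown rice are measured at month 2 and have changed like the white rice arm.
- Two of 15: (13 × 83.1 + 2 × 19.5)/15 − 19.5 = 55.1.
- Four of 15: (11 × 83.1 + 4 × 19.5)/15 − 19.5 = 46.6.

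Set against 63.6, these are the effect of assignment with some non-adherence. They answer a different question and do not measure bias.

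**5. Power if everyone is measured** (t-test, 15 per arm, SD kept at 51.46).
- Full effect of 63.6: 90.4%.
- 14% of the brown rice arm stop and change like white rice, difference 63.6 × 0.86 = 54.7: 80.2%.
- Four of 15 do so, difference 46.6: 66.9%.

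**The case against.** The strongest reply is that section 7 does not forbid later visits and that no analysis set is stated. A reader might infer that the plan prescribes a completers-only analysis, or that the outcome will certainly be lost selectively. The protocol says neither. The restriction to completers is what follows if section 7 is applied as written and the t-test is run on the available changes. Selective loss is a risk, not a stated rule.

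A reader might also infer that the bias must favour brown rice because white rice is the familiar staple. The protocol does not say that white rice is familiar. It supports only that brown rice is new to participants. Sections 3.4 and 3.6.2 put the same number of supplied meals and the same energy target on both arms, the brown rice is blended to adjust viscosity and flavour, and in an open-label trial white rice participants may stop too. The direction is not established.

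Finally, a reader might set 63.6 against 46.6 and speak of a 36% overstatement (63.6/46.6 = 1.36). That figure assigns all expected losses to diet difficulty, puts all of them in one arm and gives them no benefit from brown rice. Even then it shows dilution by non-adherence. If brown rice had no effect, that mechanism would shift nothing. Bias requires those lost to differ in prognosis, which is what step 3 assumes.

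It is also true that reasons and dates are already recorded, so discontinuation by arm can be reported without an amendment. What remains is the gap in data collection: nothing requires the month-2 primary measurement in patients who stop the diet.

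**Conclusion.** The point holds as a weakness in data collection that should be corrected. Followed as written, section 7 allows the primary outcome to go unmeasured for an exit reason that relates to the assigned diet. The size and direction of any resulting bias are unknown. It is near zero under balanced loss of equal prognosis. It is about 3 to 14 points (5% to 22% of the planned difference) if 2 to 4 of 15 are lost from one arm only and differ from completers by 0.5 to 1 SD. That range rests on assumed gaps and on one-sided loss, so it is an illustration and not a forecast. The planned sample size is not at fault. Whether a patient should stop the diet is a clinical matter and is not judged here.

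**What to change.** In section 7, separate stopping the assigned rice from withdrawing from follow-up, and leave the criteria for stopping the diet unchanged. State that every randomised participant who has not withdrawn consent to follow-up attends the already scheduled month-2 endothelial function visit, whether or not they still eat the assigned rice. Analyse all participants with a month-2 measurement in the arm to which they were assigned.

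Collect the fasting measure in all of them. The meal test in section 3.8 appears to use the rice of the participant's own group, so state whether the postprandial measure is obtained in those who no longer eat it. Report discontinuation for difficulty by arm, as information on acceptability.

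The cost is amendment wording and at most about four visits that would otherwise be skipped. The estimate may be smaller than among completers. Power stays at about 80% if 14% of the brown rice arm stop and change like white rice, but falls to about 67% if all four stoppers are in that arm. The sponsor should accept that openly as the price of keeping the randomised comparison. Patients who withdraw consent to follow-up will still be missing, and their handling can be left to the analysis plan.

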**8 Discontinuation and interruption of study**

The principal investigator should determine whether continuation of the study can be justified when significant information regarding quality, safety are newly recognized.

**9 Human rights of patients and consideration for safety and disadvantages**

**9.1 Consideration for human rights**

When implementing the present study, the Declaration of Helsinki - Ethical Guidelines for Clinical Research (2008) and the ethical guidelines for medical research involving human patients (July 31, 2008) as well as the research implementation plan should be observed.

**9.2 Ethical review committee**

This study will be conducted under ethical approval from the Ethics Committee of Shiga University of Medical Science.

**9.3 Informed consent acquisition in patients**

Prior to the start of clinical research, the principal investigator should fully inform patient candidates all pertinent aspects of the clinical research by using the informed consent form which has been approved by the ethical review committee. Written informed consent from all participants are required.

1) Objectives, significance, potential risks and benefits of the research

2) The fact that the refusal or withdrawal of consent by a research subject does not cause any disadvantage to such research subject.

3) Research subjects may withdraw their consent at any time even after they have given consent with regard that the research is commenced or continued.

4) Personal information will be protected with process of anonymization.

5) The other important procedure to protect human rights will be conducted under the guideline of Shiga University of Medical Science.

